### Randomization and allocation concealment

2.4

The allocation sequence will be generated using a permuted block design (random block sizes of 4 and 6) and will be stratified by baseline curve severity (Cobb angle ≤25° vs. >25°) to ensure balance in scoliosis severity between groups. This stratified block randomization will be implemented by an independent statistician. To ensure concealment, the sequence will be embedded into a sequentially numbered, opaque, sealed envelope (SNOSE) system, which will be prepared and safeguarded by an independent research coordinator. After baseline assessment, the coordinator will open the next consecutive envelope to assign the participant to a group. This process will ensure that recruiters and therapists remain unaware of the allocation sequence until after the participant has been assigned to a group.

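### One coordinator prepares, keeps and opens the allocation envelopes, so sealing does not conceal the next allocation from the person who assigns

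*Protocol article*

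**What the plan says.** Section 2.4 (Randomization and allocation concealment) describes permuted blocks of random size 4 or 6 within two strata, cut at a baseline Cobb angle of 25°. It names two people.

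- A statistician: "This stratified block randomization will be implemented by an independent statistician".
- A coordinator. The section says that "the sequence will be embedded into a sequentially numbered, opaque, sealed envelope (SNOSE) system", "which will be prepared and safeguarded by an independent research coordinator". It continues: "After baseline assessment, the coordinator will open the next consecutive envelope to assign the participant to a group".

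The section closes by saying that the process ensures that "recruiters and therapists remain unaware of the allocation sequence until after the participant has been assigned to a group". The coordinator is not in that list. The section does not say who places the allocations in the envelopes beyond the word for preparing them. It also does not say whether the envelopes form one numbered set or one per stratum.

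**The concern.** Allocation concealment should mean that nobody who takes part in assignment can foresee the next allocation. Envelopes achieve this when the person who opens them did not fill them. Here one role does both and also stores them in between.

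Several features of the trial make this worth attention. It has a single centre, and sections 2.4 and 2.5 together describe one-by-one assignment to arms that participants and therapists can recognise. If the assigner knew the list, the order or timing of openings could depend on which participant was waiting. The primary ANCOVA in section 2.9 adjusts for baseline Cobb angle only. It would not remove an imbalance in motivation or in likely adherence to the 10-week home programme.

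**Working it through.** The point rests on no stated figure, so the check is a reading of section 2.4 task by task.

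| Task | Who does it, per section 2.4 |
|---|---|
| Implement the stratified block sequence | Independent statistician |
| Prepare the envelopes | Independent research coordinator |
| Store the envelopes | The same coordinator |
| Open the next envelope and assign | The coordinator, after baseline assessment |
| Stated to be unaware of the sequence | Recruiters and therapists |

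1. Only one coordinator is introduced, and the sentence on opening refers back to that person with the definite article. Preparing, storing and opening therefore fall to one role.
2. Preparing envelopes from a sequence ordinarily means handling the sequence. This is an inference from one word, because the article does not describe the filling step. Nothing in the section says that the coordinator is kept from the contents.
3. Random block sizes make it harder to guess the next allocation from past ones. They give no protection against a person who has handled the list.
4. Sealing, opacity and numbering protect against people who did not prepare the envelopes. They do so for recruiters and therapists, as the section claims. They do not do so for the coordinator.
5. Exposure: the target in section 2.7 is 60 participants, and every assignment passes through this role, so 60 of 60. This counts opportunities only. The document has no input from which a bias could be derived.

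**Why the stratum wording deserves one clarifying clause.** A simulation of 60 participants with random blocks of 4 and 6 (8000 runs per scenario) compared two ways of numbering the envelopes. The measure is the absolute difference in arm sizes within one stratum. The stratum's share of participants is an assumption, because the article gives none.

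| Assumed share in the stratum | One set ignoring strata: mean difference; runs above 3 | One set per stratum: mean difference; runs above 3 |
|---|---|---|
| 30% | 2.80; 31.7% | 0.75; 0% |
| 50% | 3.13; 37.0% | 0.75; 0% |
| 70% | 2.88; 33.7% | 0.74; 0% |

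With one set per stratum, the difference cannot exceed half the largest block, 6 / 2 = 3. These figures show why the wording should be explicit. They do not show that the trial uses a single set.

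**The case against.** The strongest defence is that concealment mainly protects against foresight by those who decide who enters the trial. Section 2.4 says that recruiters stay unaware, calls the coordinator independent, and places the opening after baseline assessment. Table 1 separates enrolment from allocation. No section gives the coordinator any power over recruitment or eligibility. All of this stands, and it limits the point to role separation. It does not answer the point, because independence is not defined and the assigner is still the person who prepared the envelopes.

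Three stronger readings are tempting, and the documents do not support them.

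- **Enrolling staff can foresee allocations.** A reader might infer this from the overlap of tasks, but the section states the opposite for recruiters.
- **The envelopes form one series, so balance by severity is lost.** A reader might infer this from the statement that "the coordinator will open the next consecutive envelope to assign the participant to a group". The words fit equally well the next envelope in the participant's own stratum, and the section says that the randomization is stratified. A condensed article may also leave this detail to the full protocol.
- **A curve read near 25° could be steered into the stratum with the preferred next allocation.** This needs two series, so it cannot hold together with the single-series reading. It also needs influence over the reading. Section 2.6.1 assigns Cobb measurement to two independent readers blinded to allocation, with a third adjudicator for discrepancies above 3°, and gives the coordinator no part in it.

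**Conclusion.** The point holds as a weakness in role separation. As written, the person who makes each of the 60 assignments can know the next one, and the stated concealment does not extend to that person. This rests on two assumptions: that the coordinator who opens the envelopes is the one who prepared them, which is the plain reading, and that preparing them means seeing the allocations. If the statistician in fact supplies contents that are already sealed, the procedure is sound and only the text needs correcting.

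No bias is shown, and none can be quantified. The change is worth making because it costs little and the primary analysis could not repair selection on unmeasured characteristics afterwards. The silence on stratum sets is a matter for clarification only.

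**What to change.** Divide the tasks between the two roles already named.

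- The independent statistician who implements the sequence fills and seals the envelopes and keeps the list. That person already knows the sequence, so nobody new is unblinded. The text should confirm that this is not the analyst whom sections 2.5 and 2.8 keep blinded.
- The coordinator only receives and opens the envelopes. Before opening, the participant's code, stratum and date are written on the sealed envelope.
- One added clause states that each Cobb stratum has its own numbered set and that the next envelope is taken within the stratum.

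The cost is one task moved between existing roles, with no added staff or participants. A short amendment is needed, with ethics approval and a registry update under the article's statement on modifications. The article describes recruitment as running from June 1 to December 31, 2025 and still active. If it is still open, the remaining allocations need one re-sealing by the statistician. Where the coordinator has already handled the contents, the re-sealed set should be a newly generated continuation, since the same order in new envelopes would still be known. If recruitment has closed, the report should state who prepared and who opened the envelopes.

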### Blinding

2.5

Given the overt nature of the manual therapy intervention, blinding of participants and therapists will not be feasible. To mitigate ascertainment bias, outcome assessors (for radiographic, thermographic, and patient-reported outcomes) and the data analyst will be blinded to group assignment. Allocation will be concealed from these personnel through the use of non-identifiable participant codes until the completion of the statistical analysis. Unblinding of outcome assessors or the data analyst will not be permissible unless required for safety reasons or by the ethics committee, and any such unblinding will follow predefined institutional procedures.

### Outcomes

2.6

To minimize radiographic exposure, outcome measures will be assessed at different timepoints based on their invasiveness and clinical practicality. All outcomes will be assessed at baseline (week 0) and study completion (week 12). Additionally, to capture the immediate effects of the intensive inpatient intervention, all secondary outcomes will also be assessed immediately following the 2-week intensive intervention period (week 2).

#### Primary outcome

2.6.1

Change in the Cobb angle (degrees) of the major structural curve (defined as the curve with the largest Cobb angle), will be measured on full-length standing anteroposterior spine radiographs at weeks 0 and 12 only. A fixed tube-to-detector distance of 200 cm, with pelvic leveling blocks used if necessary to compensate for leg length discrepancy. All measurements will be performed by two independent readers blinded to participant allocation and time point. A consensus process with a third adjudicator is predefined for discrepancies greater than 3°. The intra- and inter-rater reliability of the measurements will be formally assessed using intraclass correlation coefficients (ICCs).

#### Secondary outcomes

2.6.2

Angle of Trunk Rotation (ATR), will be measured by a trunk rotation measurement device (weeks 0, 2, and 12). Axial trunk rotation (ATR) was measured using a Bunnell scoliometer (Hengjian Medical Technology Co., Ltd., Zhengzhou, China). Participants performed the forward-bending Adams test. The trunk rotation angle was systematically measured at the thoracic, thoracolumbar, and lumbar levels, and the values for each segment were recorded separately (14). A minimum of two measurements were taken for each segment per participant, and the average value was calculated and used to improve accuracy. All ATR measurements were performed by the same trained assessor.

Paraspinal surface temperature difference (ΔT) between convex and concave sides will be assessed via infrared thermography at standardized anatomical regions, including the trapezius, latissimus dorsi, and quadratus lumborum muscles (weeks 0, 2, and 12). Imaging will be performed using a short-focus uncooled far-infrared thermographic camera (Baotonghua Medical Equipment Co., Ltd., Chongqing, China). The examination room will be maintained at a constant temperature of 24 ± 2 °C with no drafts. The camera will be actived for 15 min prior to each session. Participants will acclimatize for 15 min while adopting a standardized standing posture (back to camera, head slightly lowered, feet shoulder-width apart, arms slightly abducted). Black body calibration will be performed prior to each participant. The *Δ*T for each muscle will be calculated by subtracting the mean concave-side temperature from the convex-side temperature.

Health-related quality of life, evaluated using the Society-22r(SRS-22r) questionnaire (weeks 0, 2, and 12).

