### Study design

2.1

This is a single-center, two-arm, parallel-group, randomized controlled trial. The study is being conducted at Yibin Traditional Chinese Medicine Hospital in Sichuan Province, China. This hospital is a designated National Center for Scoliosis, ensuring an adequate pool of eligible participants to achieve the target sample size within the planned timeframe. The overall trial recruitment period spans from June 1, 2025, to December 31, 2025, following ethical approval (granted in 2024) and prospective trial registration (January 6, 2025). To facilitate recruitment, advertisements have been placed in prominent locations within the outpatient hall of Yibin Hospital of Traditional Chinese Medicine and disseminated through the hospital's official WeChat account. There was no direct involvement of patients or the public in the design, conduct, or reporting of this trial. Public involvement was limited to dissemination of recruitment advertisements through the hospital's official WeChat account and its redistribution by community members.

The sponsor, Yibin TCM Hospital, is responsible for study initiation and oversight. The sponsor provided input on study design and facilitates trial management. However, all data collection is being carried out, and all future data analysis and interpretation will be performed, by the research team independently. The funder (Yibin Science and Technology Department) had no role in the study design and will have no role in the conduct, analysis, or decision to publish this study.

The study protocol was developed in accordance with the SPIRIT 2025 statement (13) and will be reported following the CONSORT (Consolidated Standards of Reporting Trials) guidelines. A completed SPIRIT checklist is provided as Supplementary Material. For each individual participant, the study timeline is defined relative to the date of randomization (designated as Week 0). The schedule of enrollment, interventions, and assessments for each participant is detailed in Table 1, and participant flow will be documented using a CONSORT diagram (Figure 1).

**Table 1 T1:** Schedule of enrollment, interventions, and assessments (SPIRIT schedule).

		STUDY PERIOD				
		Enrollment	Allocation	Post allocation	Close-out	Follow-up
TIMEPOINT	Week	0	0	1	2	12
ENROLLMENT						
Inclusion/exclusion criteria		√				
Informed consent		√				
Medical history		√		√	√	
Random allocation			√			
INTERVENTIONS						
TCM Manipulation						
Schroth Therapy						

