#### Adverse events

2.3.3

Adverse events are defined as any untoward medical occurrence in a participant, and will be categorized by severity (mild/moderate/severe) and relatedness to the intervention. Serious adverse events (SAEs) are defined as events that are life-threatening, require/prolong hospitalization, or result in significant disability or harm.

Adverse events will be systematically assessed at each study visit. Participants will be specifically asked about musculoskeletal discomfort, skin reactions, and neurological symptoms. All adverse events will be recorded, graded, and reported to the ethics committee as per institutional policy. Serious adverse events will trigger immediate review. The trial may be terminated based on the findings of this review. Participants who experience trial-related adverse events will receive free emergency medical care by the investigators.

Additionally, disease progression will be closely monitored as a key safety parameter. All participants will be regularly assessed for clinical signs of worsening, such as increased Angle of Trunk Rotation (ATR) or observable postural changes. If significant clinical deterioration is suspected, a follow-up radiograph will be obtained to confirm progression. Upon confirmation of radiological or significant clinical worsening, the study protocol includes provisions to withdraw the patient from the trial and ensure they receive appropriate standard care.

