### Statistical analysis

2.9

All analyses will be conducted using SPSS (version 20.0, SPSS Inc., Chicago, IL, USA) with a two-sided significance level of *α* = 0.05. All analyses will follow the intention-to-treat(ITT) principle. Baseline characteristics will be summarized descriptively. The primary outcome, change in Cobb angle from baseline to week 12, will be compared between groups using Analysis of Covariance (ANCOVA), adjusting for the baseline Cobb angle. Results will be presented as adjusted mean differences with 95% confidence intervals. For secondary outcomes measured at multiple timepoints (ATR, ΔT, SRS-22r), linear mixed-effects models (LMMs) will be used to analyze the longitudinal data. The models will include fixed effects for time, group, and their interaction term, with participant as a random effect. The interaction effect will be examined to test if the change over time differs between groups.

Given the multiple secondary outcomes, we will control for multiple comparisons using the False Discovery Rate (FDR) approach (Benjamini-Hochberg procedure) across the secondary endpoints. Secondary outcome *p*-values will be adjusted using FDR at the 5% level to mitigate Type I error inflation. We will treat these analyses as exploratory; any inferences from secondary outcomes will be made with caution.

Missing data will be handled under the missing-at-random assumption using full information maximum likelihood (FIML) in the mixed-effects models. A multiple imputation approach will be performed as a sensitivity analysis to verify the robustness of results.

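### Table 1 schedules ATR at weeks 0 and 2 only, while sections 2.6 and 2.6.2 require it at week 12 as well

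*Protocol article*

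**What the plan says.** Three places in the protocol article fix the ATR schedule.

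- **Section 2.6 (Outcomes)** gives the general rule: "All outcomes will be assessed at baseline (week 0) and study completion (week 12"). It then adds that "all secondary outcomes will also be assessed immediately following the 2-week intensive intervention period (week 2").
- **Section 2.6.2 (Secondary outcomes)** repeats this for ATR: it "will be measured by a trunk rotation measurement device (weeks 0, 2, and 12").
- **Table 1 (section 2.1)**, which section 2.1 names as the detailed schedule for each participant, has the header "TIMEPOINT Week 0 0 1 2 12". Its ATR row is ticked at week 0 (enrollment) and week 2, with nothing at week 12.

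The analysis depends on the repeated measurements. Section 2.9 states: "For secondary outcomes measured at multiple timepoints (ATR, ΔT, SRS-22r), linear mixed-effects models (LMMs) will be used to analyze the longitudinal data". The models contain group, time and their interaction.

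Two statements in section 2.3.3 also bear on Table 1. One is "Adverse events will be systematically assessed at each study visit". The other is "All participants will be regularly assessed for clinical signs of worsening, such as increased Angle of Trunk Rotation (ATR"). The adverse-event row of Table 1 is ticked at weeks 1 and 12 but not at week 2. A separate safety-evaluation row is ticked at weeks 2 and 12.

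**The concern.** A SPIRIT schedule is an operational table, and section 2.1 points the reader to it for the assessments. Where it disagrees with the outcome definitions, a measurement can be missed at every visit of a given kind, and for every participant.

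Here the measurement at risk is ATR at week 12, the trial's final time point and the one at which the primary outcome is read. A missed ATR cannot be recovered later. The missing-data methods in section 2.9 (full information maximum likelihood, with multiple imputation as a sensitivity analysis) would not help. They borrow from participants who were observed at a time point, and here nobody would be.

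**Working it through.** The plan states no figure to reproduce, because the question is one of time points. The check aligns each assessment row of Table 1 with the week header, cell by cell, and compares the result with the text.

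**Step 1. Align the rows.** The header has seven cells: two for labels, then weeks 0 (enrollment), 0 (allocation), 1, 2 and 12. The four outcome rows also have seven cells each.

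| Outcome | Ticks in Table 1 | Text (2.6, 2.6.1, 2.6.2) | Agree? |
|---|---|---|---|
| X-ray (Cobb angle) | 0, 12 | 0, 12 | yes |
| ATR | 0, 2 | 0, 2, 12 | **no** |
| Thermography (ΔT) | 0, 2, 12 | 0, 2, 12 | yes |
| SRS-22r | 0, 2, 12 | 0, 2, 12 | yes |

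ATR is the only outcome without a week-12 tick. Its row has the full cell count with an empty last cell, and the rows on either side show their week-12 ticks in the right place. A column lost when the PDF was read is therefore unlikely.

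**Step 2. What the analysis would lose.**

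- Under the text, ATR has 3 measurement times, 2 of them after baseline. Under the table it has 2, with 1 after baseline and none at study end.
- Planned ATR occasions for 60 participants: 60 × 3 = 180 under the text and 60 × 2 = 120 under the table. The difference of 60 is one third of the total.
- Section 2.7 allows for about 20% attrition. If all of it occurred before week 12, 60 × 0.80 = 48 participants would attend that visit. The week-12 values at stake therefore number between 48 and 60.
- If time is modelled as a factor (an assumption, since section 2.9 does not say), the group-by-time interaction has (2 − 1) × (3 − 1) = 2 degrees of freedom under the text and (2 − 1) × (2 − 1) = 1 under the table. That one degree of freedom is the group difference in change from week 0 to week 2. If time is linear, a week-12 contrast could be produced only by extrapolating 10 weeks beyond the last observation.

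**Step 3. The safety rows.**

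| Item | Table 1 | Section 2.3.3 |
|---|---|---|
| Adverse events | weeks 1, 12 | at every study visit |
| Safety evaluation | weeks 2, 12 | not defined there |
| ATR as a sign of worsening | weeks 0, 2 | assessed regularly, no weeks given |

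Week 2 is a visit with other assessments, so the adverse-event row does not match the text. The article does not say whether the safety-evaluation row covers adverse-event recording. Neither schedule places an ATR measurement between weeks 2 and 12, so the statement about regular assessment has no scheduled ATR behind it in that interval.

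**The case against.** The strongest reply is that the text settles the intent. Sections 2.6 and 2.6.2 agree with each other, section 2.9 groups ATR with the two outcomes measured at all three times, and no sentence supports leaving out week 12. One empty cell against consistent prose is most simply a forgotten tick. That stands, and it is why the loss can only be called possible. It does not remove the contradiction, because section 2.1 refers readers to the table for the schedule.

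A second reply is that Table 1 did not come through intact: the TCM manipulation and Schroth rows show no marks. The published table should therefore be checked. Those are intervention rows, however, and the other three outcome rows match the text exactly.

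A third reply is that this is a journal article, and site staff may work from a full protocol and case report forms that are not shown. Section 2.8 also describes monthly data quality audits. This is fair. The documents do not show which schedule staff follow, so a complete loss of week-12 ATR is the worst case and not a derived result.

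Two stronger readings are tempting, and the documents do not support them.

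- A reader might infer that the missing tick prevents worsening from being detected during the home phase. Adding the tick would put no ATR measurement between weeks 2 and 12. At week 12 the radiograph measures the curve directly. Section 2.3.3 also does not rely on ATR alone: it names "clinical signs of worsening, such as increased Angle of Trunk Rotation (ATR) or observable postural changes", with a radiograph when deterioration is suspected.
- A reader might infer that adverse events from the manipulation phase would be asked about only at week 12, up to 10 weeks late. Table 1 ticks a safety evaluation at week 2 and medical history at weeks 1 and 2. Participants are inpatients under twice-daily supervision during that phase, and they receive weekly calls afterwards.

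**Conclusion.** The contradiction is real: Table 1 gives ATR at weeks 0 and 2, and sections 2.6 and 2.6.2 give weeks 0, 2 and 12. If the table is followed, one of three secondary outcomes has no week-12 value and its model can address only the immediate post-inpatient change. This conclusion assumes that the published table matches the text read from the PDF. The size of the loss depends on which schedule the site uses, which the documents do not show.

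The severity is minor to moderate. Section 2.9 treats the secondary analyses as exploratory, and the Cobb angle comparison and the sample size are untouched. What lifts it above a typographical remark is that a missed week-12 ATR is permanent, while preventing it costs almost nothing. The adverse-event row and the statement on regular assessment are minor inconsistencies to reconcile, with no demonstrated harm.

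**What to change.** 1. Correct Table 1 so that ATR is ticked at week 12, in line with sections 2.6 and 2.6.2, after checking the published table.
2. Confirm that the case report forms and the site schedule carry a week-12 ATR field, and notify site staff if they do not. Recruitment is planned to end on December 31, 2025, so the last week-12 visits fall 84 days later, around March 25, 2026.
3. If any participants have already passed week 12 without an ATR measurement, record how many and report it with the ATR analysis.
4. Reconcile the adverse-event row of Table 1 with section 2.3.3, and say how the safety-evaluation row relates to adverse-event recording. Reconcile the statement on regular assessment for worsening with the visits that exist between weeks 2 and 12.

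The cost is a table correction, a check of the forms and a short site notice. No new visit is needed, because the radiograph, thermography and SRS-22r are already taken at week 12.
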